**Research Plan:**

**Study centre**: Base Hospital Chilaw, Anuradhapura, Peradeniya for a period of 12 months. It is an original study, **A randomized, open label, controlled clinical trial.** A total 240 patients will be recruited in this study.

A randomized, double-blind, controlled clinical trial with two parallel groups:

- 10 vials of polyvalent antivenom administered in Normal saline (500ml) over 20 minutes*
- 10 vials of polyvalent antivenom administered in Normal saline (500ml) over 2 hours*

If the patient is administered more than 10 vials then this will be given at the same rate =10 vials over 20 minutes or 2 hours (Although the volume and dilution can be modified for convenience).For example 20 vials given over 40 minutes in 500 ml of Normal saline.

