**ii. Detailed description of the research method.**

All patients bitten by a snake will be eligible for the study and will be approached at the time of admission, however they will not formally enter the interventional trial until the decision is made to administer antivenom. All eligible patients will have baseline clinical data collected, including clinical symptoms, signs and a 20 minute whole blood clotting test (20 WBCT). Baseline blood will be collected (see below). When a decision to administer antivenom is made, the patient will be randomized to one of the two parallel treatment arms. Patients in the first treatment group will receive 10 vials of antivenom in 500 ml of normal saline over 20 minutes [alternatively 20 vials of antivenom in 500 ml of normal saline over 40 minutes] Patients in the second treatment group will receive 10 vials of antivenom in 500 ml of normal saline over 2 hrs [alternatively 20 ampoules of antivenom in 500 ml over 4 hours.]

Randomisation will be done by computer in blocks of four (eg. AABB, ABAB etc.) using Microsoft Excel. The computer generated list will be used to randomize pieces of papers to sequentially ordered envelopes with the wording “20 minute infusion” or “2 hour infusion”

Patients will be closely observed for the four hour period following the commencement of administration of antivenom. The patient will be put on a cardiac monitor for this period if possible. For the first hour, HR, BP, RR, oxygen saturation and temperature will be measured every 5 minutes and then every hour for the remainder of the four hours. Patients will be observed for evidence of an allergic reaction using the Brown grading system,(10) including auscultation of the chest. Allergic reactions will be treated as per the current protocol of antivenom reactions with intravenous fluids and 0.5 mg of intramuscular adrenaline into the lateral thigh (or upper arm if not possible).

A 15 mL sample of blood will be taken using a sterile technique (syringe and needle) from each patient.

- 1. The 15mL sample will be divided between one serum (red top tube), one EDTA tube (purple top) and one plasma citrate (blue top) tube.
  2. The serum tube will be spun and the serum aliquoted into 3 portions and frozen.
  3. The citrate plasma tube will be immediately double spun and then aliquoted into two separate tubes and immediately frozen.
  4. The EDTA tube will be spun and aliquoted into two separate containers.

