**Description of all medical procedures and safety measures**

All eligible patients will have baseline clinical data collected, including clinical symptoms, signs and a whole blood clotting test (WBCT). Baseline blood will be collected (see below).

Patients in the first treatment group will receive 10 vials of antivenom in 500 ml of normal saline over 20 minutes. Patients in the second treatment group will receive 10 vials of antivenom in 500 ml of normal saline over 2 hrs. Patients will be closely observed for the four hour period following the commencement of administration of antivenom. The patient will be put on a cardiac monitor for this period if possible. For the first hour, HR, BP, RR, oxygen saturation and temperature will be measured every 5 minutes and hourly for the remainder of the four hours. Patients will be observed for evidence of an allergic reaction using the Brown grading system, including auscultation of the chest. Allergic reactions will be treated as per the current protocol of antivenom reactions with intravenous fluids and adrenaline.

A 15 ml sample of blood will be taken using a sterile technique (syringe and needle) from each patient consenting to the study. Normal coagulation studies will be performed on samples for patients who developed coagulopathy. Creatine kinase will be measured in patients with Russell’s viper bite. Serial mast cell tryptase, complement and anaphylactic mediators will be measured in all patients who receive antivenom by the laboratory of Assoc. [name] in Western Australia. Urine will be collected in patients with Russell’s viper bite.

Throughout the trial, the patient will remain under the responsibility of the admitting consultant. Both study and host hospital clinicians will report to this individual.

**Primary outcome:** proportion with severe systemic allergic reactions (grade 3 by Brown grading system) within 4 hours of commencement of antivenom.

**Secondary outcomes:** proportion with elevated mast cell tryptase: proportion with elevated complement; hospital length of stay; proportion with mild and moderate allergic reaction (grade 1 and 2 Brown grading); and proportion with delayed administration of further antivenom therapy. Proportion developing serum sickness will be determined in a smaller number because follow up after discharge is difficult in the rural hospital setting.

Brown Grading System for systemic allergic reactions.

| Grade | Clinical Effects |
| --- | --- |

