| **I**  Mild(skin and subcutaneous tissues only) | Generalized erythema,urticaria, periorbital oedema or angioedema. |
| **2**  Moderate(features suggesting respiratory, cardiovascular, or gastrointestinal involvement) | Dysponea,stridor,wheeze,nausea,vomiting,  dizziness (pre syncope) diaphoresis, chest or throat tightness or abdominal pain. |
| **3**  Severe (hypoxia, hypotension or neurological compromise) | Cyanosis or SpO2 less than or equal 92% at any stage, hypotension,(SBP<90mmHg in adults)confusion, collapse, LOC or incontinence. |

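### Readings drop from every 5 minutes to hourly after the first hour, so brief grade 3 falls in pressure or saturation can be missed more often in the slow arm

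*Protocol*

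**What the plan says.** **Schedule.** The Protocol, section ii (Detailed description of the research method), states that after the start of antivenom "HR, BP, RR, oxygen saturation and temperature will be measured every 5 minutes and then every hour for the remainder of the four hours"; the 5-minute interval applies to the first hour. The section on medical procedures and safety measures repeats this: readings "will be measured every 5 minutes and hourly for the remainder of the four hours". The schedule is the same in both arms.

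**Infusion times.** Section ii gives the fast arm 10 vials "over 20 minutes [alternatively 20 vials of antivenom in 500 ml of normal saline over 40 minutes", and the slow arm 10 vials "over 2 hrs [alternatively 20 ampoules of antivenom in 500 ml over 4 hours". The Research Plan keeps the rate per vial fixed, so the duration grows with the dose.

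**Outcome.** The primary outcome is the proportion with a Brown grade 3 reaction within 4 hours of starting antivenom. Two grade 3 criteria are measured thresholds: systolic pressure below 90 mmHg in adults, and "SpO2 less than or equal 92% at any stage". The others (cyanosis, confusion, collapse, loss of consciousness, incontinence) can be seen without a scheduled reading.

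**Other observation.** Both sections also provide close observation over the four hours, grading of reactions with chest auscultation, and a cardiac monitor where feasible.

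**The concern.** The reading schedule follows the clock, while exposure to antivenom follows the arm. By minute 60 a fast-arm patient on 10 or 20 vials has received the whole dose under 5-minute readings. A slow-arm patient has received half of it or a quarter, and the rest is given under hourly readings.

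This matters because of how grade 3 is reached. The sample size section names hypotension as the most common form of the moderate and severe reactions in earlier studies. Hypotension without outward signs is found only if pressure is taken. If some slow-arm reactions start later because the antivenom arrives later, the chance of recording them is lower, and the slow arm would look safer than it is. That is the direction of the main hypothesis.

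The list of methods against bias (under the inclusion and exclusion criteria) relies on objective outcomes, prospective recording by the study team and intention-to-treat analysis. None of these recovers a reading that was never taken. Nor can unscheduled readings be assumed equal by arm: the Research Plan calls the trial both open label and double-blind, and a 20-minute and a 2-hour infusion are easy to tell apart at the bedside.

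**Working it through.** **Inputs from the Protocol.** Readings every 5 minutes to minute 60, then hourly to minute 240 (sections cited above). Infusion times of 20 and 120 minutes (10 vials) or 40 and 240 minutes (20 vials). Rates of 50% and 30%, alpha 5%, power 80%, 103 per arm (sample size section).

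**The plan's own figure.** For 50% against 30%, two-sided 5% and 80% power, the uncorrected two-proportion formula gives 93 per arm, and the continuity-corrected one gives 103. The stated 103 is reproduced. The Protocol does not state sidedness; two-sided is the reading that fits.

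**Share of the infusion under 5-minute readings** = min(60, T)/T, with T the infusion time in minutes.

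| Dose | Fast arm | Slow arm | Scheduled readings in the slow infusion after minute 60 |
|---|---|---|---|
| 10 vials | 20/20 = 100% | 60/120 = 50% | 1 |
| 20 vials | 40/40 = 100% | 60/240 = 25% | 3 |

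Fast-arm coverage stays at 100% up to 30 vials (60 minutes).

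**Chance that a scheduled reading catches an episode of length L** = min(1, L/interval). For an assumed L of 15 minutes this is 1 on 5-minute readings and 15/60 = 25% on hourly ones. For L of 10 or 30 minutes, hourly readings catch 17% or 50%.

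**Effect on the comparison (illustration).** Assume the same true grade 3 risk p in both arms and all fast-arm events detected. Let f be the share of slow-arm events starting after minute 60, and s the share of events visible only on a scheduled reading. Then

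recorded slow-arm rate = p × [1 − f × s × (1 − 15/60)].

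For f = s = 25% and p = 50%: 0.5 × (1 − 0.25 × 0.25 × 0.75) = 47.7%. For f = s = 50%: 0.5 × (1 − 0.5 × 0.5 × 0.75) = 40.6%.

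With Δ the spurious difference and SE = √[p(1−p)/103 + q(1−q)/103], where q is the recorded slow-arm rate, the chance of p<0.05 is Φ(Δ/SE − 1.96) + Φ(−Δ/SE − 1.96). In the first case Δ/SE = 0.0234/0.0696 = 0.34, giving 0.052 + 0.011 = 6.3%. In the last, 0.0938/0.0691 = 1.36, giving about 27%.

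| f | s | Recorded slow rate (true 50%) | Spurious reduction, points | False-positive rate, p = 50% | False-positive rate, p = 20% (assumed) |
|---|---|---|---|---|---|
| 25% | 25% | 47.7% | 2.3 | 6.3% | 5.3% |
| 25% | 50% | 45.3% | 4.7 | 10.3% | 6.4% |
| 50% | 25% | 45.3% | 4.7 | 10.3% | 6.4% |
| 50% | 50% | 40.6% | 9.4 | 27% | about 11% |

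The value f = 50% is what uniform onset over a 2-hour infusion would give. The 20% baseline is included because the sample size section ties 50% to grades 2 and 3 together, whereas the primary outcome is grade 3 alone.

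**The case against.** The strongest reply is that the schedule and the 4-hour outcome window are both set by the clock and are identical in the two arms. Fast-arm reactions after minute 60 are read hourly too. A difference in detection needs three things together: slow-arm events that start later, that last well under an hour, and that nothing but a scheduled reading would reveal. The Protocol gives no data on onset or duration. Patients are watched for four hours, the study team is on duty around the clock and records outcomes prospectively, and nothing bars an extra pressure or saturation check when a patient looks unwell. The events at risk are therefore brief and clinically silent.

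Most of this stands, and it limits the claim. A reader might infer that the schedule shows grade 3 events *are* under-detected in the slow arm. The document does not show that; it shows that they can be. A reader might also take the extreme case in the formula above, with half of the events late and every event visible only on a reading: the slow arm would then record 31% and the false-positive rate would be about 79%. That requires that no grade 3 reaction is ever noticed clinically, which does not fit the observation plan or the visible signs in the grading table.

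What does not stand is that the safeguards close the gap. The monitor is conditional and need not record blood pressure, close observation carries no reading interval, and grade 3 can be met by a threshold value alone.

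**Conclusion.** The point holds as a risk of unequal ascertainment of the primary outcome, not as a demonstrated bias. The coverage figures are exact: 100% of the fast infusion against 50% or 25% of the slow one. If slow-arm reactions tend to start later, the direction is clear and favours the hypothesis of a fall from 50% to 30%.

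The size is not known. With 103 per arm, 50% true risk in both arms and 15-minute episodes, the two-sided false-positive rate is about 6% (25% late, 25% reading-only) to 27% (50% late, 50% reading-only), against a nominal 5%. With an assumed 20% baseline the same cases give about 5% to 11%. These are illustrations and not bounds: a larger late share, as could arise with 4-hour infusions, would raise them, and the Protocol does not say how many patients would receive 20 vials. The sample size is not affected. This is an inexpensive improvement worth making before recruitment, since readings not taken cannot be recovered in the analysis.

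**What to change.** 1. For outcome ascertainment, take blood pressure and oxygen saturation more often after hour 1, in both arms, to the end of the 4-hour window. Every 15 minutes is one workable choice: a 15-minute episode is then caught with probability 15/15 = 1 instead of 25%, and a 10-minute one with 10/15 = 67% instead of 17%. Keep the 5-minute readings of the first hour. Infusion and treatment of reactions are unchanged.
2. Amend section ii and the medical procedures and safety section together, so that both give the same schedule.
3. Keep the primary outcome as grade 3 at any time within 4 hours. Restricting it to a 15-minute grid would discard real first-hour events and contradict the grading table.
4. Add a sensitivity analysis that counts threshold-only grade 3 events on a common 15-minute grid in both arms, with clinically evident grade 3 events counted whenever they occur. This addresses the remaining difference between 5-minute and 15-minute reading. Define threshold-only in advance as grade 3 met by a pressure or saturation value without any other grade 3 sign.

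**Cost.** From hour 1 to hour 4 there would be 12 sets of readings instead of 3, about 9 more per patient, plus a protocol and case-record change. The workload is modest for a team already on duty 24 hours a day. The sample size stays at 103 per arm.

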**How the sample size was determined:**

In two previous studies approximately 50% of patients administered antivenom had a Brown grade 2 or 3 systemic allergic reaction (most commonly hypotension). (4,8) A reduction (absolute) of 20% would be clinically significant and would be sufficient to warrant the use of premedication. In order to detect whether premedication reduces the rate of allergic reactions from 50% to 30%, with a significant level (alpha) of 5% and a power of 80%, a minimum of 103 patients must be recruited to each arm of the trial (i.e. A total of 206 patients). To ensure appropriate recruitment and loss of patients the aim will be to recruit 240 patients.

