**iii. Description of data analysis procedure**

The RCT aims to determine the effectiveness of two different infusion rates of antivenom administration. The primary analysis will be done by intention-to-treat using the chi squared test for the primary outcome (or Fisher’s exact test if appropriate) and for other dichotomous outcomes. The relative risk (and risk reduction)and absolute risk reduction (with 95% confidence intervals) will also be calculated. For the outcomes (mainly the primary outcome) where the time –to-event is recorded, the log rank test will be used to compare treatment groups.

Analysis of trends in treatment effect for factors ‘initial dose of antivenom’ and ‘use of antivenom prior to hospital admission’ will also be performed using statistical modeling techniques.

Admission blood samples will be retrospectively analysed to confirm the identity of the snake. The primary analysis will then be repeated to correct for this.

The main hypothesis is that a slower infusion rate of antivenom (10 vials over 2 hours versus 20 minutes) will reduce the rate of all severe allergic reactions following antivenom administration from 50% to 30%.

We also want to determine if the severity of antivenom reaction is inversely related to the severity of envenoming. This will be done by comparing the concentration of venom in patient’s blood (ELISA) to severity of reaction for individual snake species.

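### The sample size rests on a 50% rate of grade 2 or 3 reactions, but the primary outcome is grade 3 alone, so the stated 80% power is unsupported for the primary comparison

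*Protocol*

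**What the plan says.** The section on how the sample size was determined reports that in two previous studies "approximately 50% of patients administered antivenom had a Brown grade 2 or 3 systemic allergic reaction", and notes that hypotension was the commonest feature. It continues: "A reduction (absolute) of 20% would be clinically significant" and "would be sufficient to warrant the use of premedication". The powered contrast is whether premedication "reduces the rate of allergic reactions from 50% to 30" per cent, "with a significant level (alpha) of 5% and a power of 80" per cent, giving "a minimum of 103 patients must be recruited to each arm of the trial (i.e. A total of 206 patients". The recruitment target is raised to 240 to allow for losses.

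The primary outcome, under the description of medical procedures and safety measures, is the "proportion with severe systemic allergic reactions (grade 3 by Brown grading system) within 4 hours of commencement of antivenom". Grades 1 and 2 are secondary outcomes. The Brown table that follows treats grade 2 (moderate) and grade 3 (severe) as separate categories and lists systolic pressure below 90 mmHg under grade 3.

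The data analysis section states the main hypothesis that slower infusion "will reduce the rate of all severe allergic reactions following antivenom administration from 50% to 30" per cent.

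**The concern.** The same pair of figures, 50% and 30%, carries three labels: grade 2 or 3 reactions where the rate is sourced, allergic reactions without a grade where the calculation is stated, and severe reactions in the main hypothesis. Only the first has a source. Grade 3 is a subset of grade 2 or 3, so its rate equals 50% only if nobody in the source studies had grade 2 as their worst grade. The protocol does not say that.

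The difference worth detecting is also argued only for premedication, which this trial does not test.

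The stated power matters here because the Background says rapid infusion would be the more appropriate approach if it does not increase the reaction rate. A non-significant result could therefore be taken as support for rapid infusion. A reader weighing such a result needs to know what power the primary comparison really had.

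**Working it through.** **Inputs from the protocol.** Rates 50% and 30%; alpha 5% (sidedness not stated; two-sided reproduces the figure); power 80%; 103 per arm; 240 in total, that is 120 per arm. The primary test is chi-squared, or Fisher's exact test if appropriate.

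**Assumed.** Grade 3 control rates of 25% to 45%. The protocol gives none. The upper limit is 50%, and the remark about hypotension suggests a sizeable share was grade 3 without fixing it.

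**Step 1: reproduce 103.** With mean rate 0.40 and difference 0.20:

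n0 = [1.960·√(2·0.40·0.60) + 0.8416·√(0.50·0.50 + 0.30·0.70)]² / 0.20² = (1.3579 + 0.5708)² / 0.04 = 93.0.

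With continuity correction: n = (n0/4)·[1 + √(1 + 4/(n0·0.20))]² = 23.25·(1 + 1.1023)² = 102.8, so 103 per arm.

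The stated figure is matched exactly, but only with the correction.

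**Step 2: power formula on the same basis.** With d the difference, m the mean of the two rates p1 and p2, and n per arm:

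z = {d − 1/n − 1.960·√[2m(1−m)/n]} / √{[p1(1−p1) + p2(1−p2)]/n}, and power = Φ(z).

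For 50% to 30% at n = 103 this gives 80.1%. Dropping the 1/n term gives 83.9%. The protocol's 80% is therefore a continuity-corrected figure, and the results below keep the correction so that they can be compared with it.

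**Step 3: what carries over to grade 3?** At a 50% base rate, a 20-point drop and a relative risk of 0.6 (30/50) are the same thing. At any lower rate they differ.

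Worked examples at 103 per arm:
- 40% to 24% (relative risk 0.6): z = (0.16 − 0.0097 − 0.1274)/0.0640 = 0.357, power 64.0%.
- 40% to 20% (20 points): z = (0.20 − 0.0097 − 0.1252)/0.0623 = 1.045, power 85.2%.

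| Assumed grade 3 control rate | Relative risk 0.6: slow-arm rate | Power at 103 (120) | 20-point drop: slow-arm rate | Power at 103 (120) | Relative reduction implied by 20 points |
|---|---|---|---|---|---|
| 45% | 27% | 72.5% (79.5%) | 25% | 82.2% (88.1%) | 44% |
| 40% | 24% | 64.0% (71.5%) | 20% | 85.2% (90.5%) | 50% |
| 30% | 18% | 45.7% (52.6%) | 10% | 93.3% (96.5%) | 67% |
| 25% | 15% | 36.6% (42.6%) | 5% | 97.4% (98.9%) | 80% |

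If the grade 3 rate is below 20%, a 20-point drop is impossible.

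**Step 4: effects between the two columns.** The same formula at 103 per arm gives 80.8% for 40% to 21% and 82.5% for 25% to 9%. At these base rates, 80% power can be reached with somewhat less than the full 20 points.

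**The case against.** The strongest reply is that the protocol states its important difference in absolute terms. It never mentions a relative reduction; the 0.6 is only implied by 50% and 30%. On the plan's own criterion a lower base rate raises power, as the 20-point columns show. That point stands, and it rules out a tempting inference: that the trial is underpowered and a non-significant result is likely. The documents do not support this, because they fix neither the grade 3 rate nor the form of the effect. Even with a relative risk of 0.6, power at 120 per arm is 79.5% at a 45% rate, and the remark about hypotension points towards the higher rates. What the reply cannot do is restore the 80%. A 20-point drop from 30% or 40% removes one half to two thirds of severe reactions, against the 40% reduction implied at the planning rate, and the protocol offers no support for an effect of that size.

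A second inference is that the calculation belongs to a different treatment because it speaks of premedication. That goes too far: the data analysis section ties the same 50% to 30% to infusion over 2 hours versus 20 minutes. The word does not alter the sample size. What remains is a wording error and a threshold argued only for premedication.

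A third reply is that the main hypothesis itself gives 50% for severe reactions. It does, but without a source and against the definition attached to that figure where it is sourced.

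**Conclusion.** The concern holds as an inconsistency of endpoint, not as an error of arithmetic. The 103 per arm is right for a 50% versus 30% comparison, and the sourced 50% is a grade 2 or 3 rate. For the grade 3 primary outcome, the stated 80% power is unsupported.

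The size and direction of the change in power cannot be settled from the protocol. Over assumed grade 3 rates of 25% to 45%, continuity-corrected power at 103 per arm runs from 36.6% to 72.5% if a relative risk of 0.6 carries over, and from 82.2% to 97.4% if the 20-point drop carries over. The extra 17 per arm in the recruitment target offsets the first case only in part, and they are there to cover losses.

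These figures rest on the normal approximation with continuity correction, a two-sided 5% level and equal arms. An endpoint, a planning rate and a power figure that the protocol itself states should agree before the power is relied on.

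**What to change.** Make the sample-size section, the main hypothesis and the primary outcome refer to one endpoint:

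- Keep grade 3 within 4 hours as primary, and state an assumed grade 3 control rate with its source, or as an assumption with a range.
- Restate power, or the detectable difference, at 103 to 120 per arm under both an absolute and a relative effect, using one version of the test throughout.
- Present 50% to 30% as the grade 2 or 3 figure, and reword the main hypothesis so that it does not attach those rates to severe reactions.
- Replace the references to premedication in the sample-size section, and justify the important difference for infusion rate.

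The cost is protocol wording. The stated power may become less favourable. No extra patients are needed to make the change.
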